## Data Availability

No new data were created or analyzed in this study. Data sharing is not applicable to this article.

## Abbreviations

The following abbreviations are used in this manuscript:

ABS	Agitated Behavior Scale
AE	Adverse Events
AER	Adverse Events Report
ANCOVA	Analysis of Covariance
BDNF	Brain-Derived Neurotrophic Factor
BP	Blood Pressure
CRS-R	Coma Recovery Scale-Revised
CT	Computerized Tomography
DRS	Disability Rating Scale
EEG	Electroencephalogram
eDoC	emergence from Disorder of Consciousness
FDG-CCS	Fondazione Don Gnocchi-Clinical Complication Scale
GFAP	Glial Fibrillary Acid Protein
HR	Heart Rate
IQR	Inter-Quartile Range
LCF	Levels of Cognitive Functioning
LMM/GLMM	Linear Mixed-effects Models/Generalized Linear Mixed-effects Models
LP-HP	Low Pass-High Pass
MAR	Missing at Random
MAS	Modified Ashworth Scale
MCS	Minimally Conscious State
MNAR	Missing Not At Random
MRC	Medical Research Council scale
mBI	modified Barthel Index
NCS-R	Nociception Coma Scale-Revised
NF-L	Neurofilament Light chain
pDoC	prolonged Disorder of Consciousness
RCT	Randomized Controlled Trial
REDCap	Research Electronic Data Capture
sABI	severe Acquired Brain Injury
SPIRIT	Standard Protocol Items: Recommendations for Interventional Trials
SUS	System Usability Scale
TPI	Time Post-Injury
TV	Traditional Verticalization
VEM	robotic VErticalization and Mobilization
VS/UWS	Vegetative State/Unresponsive Wakefulness Syndrome

## Appendix A

**Table A1 jcm-14-06628-t0A1:** List of the tasks available on Erigo^®^Basic and Erigo^®^PRO (Hocoma, Volketswil, Switzerland) and employed for the VEM training. The only difference between Erigo^®^Basic and Erigo^®^PRO is the presence of functional electric stimulation and adjustable hip extension/flexion angle in PRO version, which, however, will not be used in the current trial. Technical data could be found here: https://www.hocoma.com/landing-page/erigo-technical-datasheet-landing/?_gl=1*1onln9k*_up*MQ..*_ga*MTgxOTA2NDQwOS4xNzU0OTIxNjE1*_ga_TJ0VMN8KZJ*czE3NTQ5MjE2MTQkbzEkZzEkdDE3NTQ5MjE2MjMkajUxJGwwJGgw (accessed on 1 September 2025).

Original Name	English Name	Description
Sinus	Sinus	Walking with additional high strike phase, step per minute range from 8 to 80
Andatura	Walking	Walking, step per minute range from 8 to 80
Alternato	Alternate	Simple stepping, step per minute range from 8 to 80

## Appendix B

*Prohibited Medications Increasing the Risk of Orthostatic Hypotension*

The following Table A2 enlists all medications that may potentially increase the risk of orthostatic hypotension, particularly in bedridden or immobilized patients. These drugs may compromise the safety of verticalization.

To ensure protocol integrity and patient safety, all such interventions are prohibited during the trial period; patients already receiving any of these interventions at screening should be considered ineligible for enrollment (exclusion criteria). These drugs must not be initiated at any time between T0 and T2; be tapered or discontinued before enrollment, allowing for a minimum washout of 4× the drug’s half-life; be resumed until the study follow-up is complete. The initiation of any listed medication during the study period will be considered a protocol violation. Source for the estimated half-life was the Italian Medicines Agency (AIFA; https://api.aifa.gov.it (accessed on 1 September 2025)).

**Table A2 jcm-14-06628-t0A2:** Prohibited medications increasing the risk of orthostatic hypotension.

Drug Class	Examples	Estimated Half-Life	Recommended Action
Loop diuretics	Furosemide	1–1.5 h (up to 24 h in renal failure)	Consider holding 12–24 h prior
Beta-blockers	Metoprolol, Atenolol	Metoprolol: 1–9 h Atenolol: Up to 24 h	Reduce dose or hold 24 h prior
Alpha-blockers	Doxazosin, Prazosin	~22 h	Stop 48 h before
ACE inhibitors	Enalapril, Lisinopril	11–24 h	Consider holding 24–48 h before
ARBs	Losartan	up to 24 h	Consider holding 24–48 h before
Tricyclic antidepressants	Amitriptyline, Nortriptyline	25 h	Hold 48–72 h before
Antipsychotics	Risperidone, Quetiapine, Olanzapine	3–30 h (depends on drug)	Review or suspend 48 h before
Dopaminergic agents	Pramipexole, Ropinirole	>6 h	Taper or review
Benzodiazepines/Sedatives	Lorazepam, Diazepam	Lorazepam: 12–16 h; Diazepam: >30 h	Hold 24–72 h before
Nitrates	Nitroglycerin, Isosorbide	1–5 h	Suspend the day before
Opioids	Morphine, Oxycodone	Morphine: 2–4 h; Oxycodone: >12 h	Hold 24–48 h before if possible

Abbreviations: ACE = Angiotensin-Converting Enzyme Inhibitors; ARBs = Angiotensin Receptor Blockers.

*Proscribed Drugs*

*Caution/“record and adjust” medications*

These “Proscribed” medications are all drugs that may influence cognitive status, attention, arousal, or level of consciousness. These pharmacological effects can significantly bias the assessment of cognition and reduce the validity of intervention primary outcomes. These medications not necessarily need to be discontinued before the intervention, but must be carefully documented (“recorded”) in the study records (on REDCap registry), and may require adjustments (“adjusted”) in timing or administration according to clinical condition and safety (e.g., give in the evening after intervention or clinical-EEG assessment instead of morning, temporarily reduce dose, etc.), to avoid interference with primary outcomes (e.g., alertness, cognitive performance). If the patient is under one of these drugs at study entry, the patients are eligible if they keep the same dosage during the study protocol. If the dosage changes, or one of these drugs needs to be started or discontinued, this is considered as a protocol violation.

The following Table A3 provides a comprehensive overview of CNS-active drugs that may negatively impact cognitive performance [22,49]. It includes their expected cognitive effects, approximate half-lives, and recommended timing for possible tapering or discontinuation before the intervention onset. These recommendations are based on pharmacokinetics (typically 4× half-life for elimination of clinical effect) and clinical safety considerations.

Table A4 summarizes both pharmacological and non-pharmacological interventions that have been proposed to enhance recovery of consciousness and cognitive functioning in patients with severe brain injury, as outlined by Edlow et al. [21]. While a limited number of interventions (such as amantadine and transcranial electrical stimulation) are supported by moderate-to-high level evidence from RCTs, the majority remain experimental, supported only by preliminary data (e.g., case reports, early-phase trials).

**Table A3 jcm-14-06628-t0A3:** Proscribed medications negatively impacting cognitive performance.

Drug Class	Examples	Half-Life (approx.)	Cognitive/CNS Effects	When to Stop Before Cognitive Tasks/Intervention
Z-drugs	Zolpidem	2–3 h	Memory alteration, confusion	12–24 h before
Typical Antipsychotics	Haloperidol	14–26 h	Rigidity, slowed cognition, delirium	≥3–4 days before
Sedating Antidepressants	Mirtazapine, Trazodone	Mirtazapine: 20–40 h; Trazodone: 5–13 h	Sedation, psychomotor slowing	Mirtazapine: 2–3 days; Trazodone: 24–48 h before
Anticholinergics	Oxybutynin, Trihexyphenidyl	2–16 h	Confusion, disorientation	≥2–3 days before
Antihistamines	Diphenhydramine	4–9 h	Sedation, attention deficit	24–48 h before
Antiepileptics	Levetiracetam, Carbamazepine	Levetiracetam: 6–8 h; Carbamazepine: 12–17 h	Slowed processing, dizziness	≥2–4 days before
Parkinson’s Drugs	Levodopa	1–2 h	Hallucinations, confusion	Taper 24–48 h before if possible
Corticosteroids	Dexamethasone, Prednisone	Dexamethasone: 3–4.5 h; Prednisone: 3–6 h	Insomnia, psychosis, delirium (high doses)	Avoid night doses; consider tapering 48 h before
Chemotherapeutics	Methotrexate, Cisplatin	Methotrexate: ~3–10 h Cisplatin: variable	Confusion, memory loss	Not suspendable; monitor symptoms
Barbiturates	Phenobarbital	80–100 h	Deep sedation, cognitive decline	≥7–10 days before
Melatonin (high dose)	Melatonin	20–50 min	Mild sedation, drowsiness	≥6–8 h before

Abbreviations: CNS = Central Nervous System.

**Table A4 jcm-14-06628-t0A4:** Proscribed intervention supporting cognitive recovery in severe acquired brain injury.

Category	Intervention	Evidence Level
Pharmacological	Amantadine	★★★★☆—Supported by one RCT in subacute traumatic brain injury
	Zolpidem	★★☆☆☆—Case reports and EEG, PET studies; paradoxical responders
	Baclofen, Midazolam	★☆☆☆☆—Theoretical rationale; anecdotal use; limited case data
	Amitriptyline, Desipramine, Protriptyline	★☆☆☆☆—Sparse data; potential cognitive modulation via noradrenergic/cholinergic systems
	Modafinil	★★☆☆☆—Case reports and early-phase trials suggest increased arousal
	Psilocybin	☆☆☆☆☆—Experimental stage; partial agonist of the 5-HT2A serotonergic receptor in the central nervous system.
Neuromodulation	Deep Brain Stimulation	★★☆☆☆—Positive results in small case series; no large RCTs
	Transcranial Electrical Stimulation	★★★☆☆—Some positive RCTs (30–50% response in MCS patients)
	Transcranial Magnetic Stimulation	★☆☆☆☆—Inconsistent results; limited RCT evidence
Mechanical	Low-Intensity Focused Ultrasound Pulsation	★★☆☆☆—Early-phase studies and case reports; promising but experimental
Sensory	Auditory, tactile, vestibular stimulation	★★☆☆☆—Some RCTs show behavioral or autonomic improvements
	Personalized music therapy	★★☆☆☆—Small studies and clinical reports suggest potential benefits
Regenerative	Stem cell therapies (IV or intrathecal)	★★☆☆☆—Phase I studies suggest safety and preliminary efficacy
	Neurogenesis, gliogenesis, axonal regrowth	☆☆☆☆☆—Preclinical and conceptual stage

Abbreviations: 5-HT2A = 5-Hydroxytryptamine 2A receptor; EEG = Electroencephalography; MCS = minimally conscious state; PET = Positron Emission Tomography; RCT = randomized control trial; ★★★★☆ = Consistent evidence from RCTs or meta-analyses; ★★★☆☆ = Moderate evidence from small RCTs or cohort data; ★★☆☆☆ = Limited evidence (case series, mechanistic); ★☆☆☆☆ = Anecdotal or theoretical only; ☆☆☆☆☆ = Experimental/preclinical.

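### Appendix B requires a minimum washout of four half-lives before enrolment, but several hold times in Table A2 fall short of it on the table's own half-lives

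*Protocol article*

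**What the plan says.** Table 2 makes the presence of a prohibited drug an exclusion criterion and refers to Appendix B. The Appendix B text before Table A2 states that "patients already receiving any of these interventions at screening should be considered ineligible for enrollment (exclusion criteria". It then provides a route to later entry: the drug is to "be tapered or discontinued before enrollment, allowing for a minimum washout of 4× the drug’s half-life". The rule applies drug by drug and is counted to enrolment.

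Table A2 gives an estimated half-life and a recommended action for each drug class. The actions include:

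- Alpha-blockers (about 22 h): "Stop 48 h before".
- Tricyclic antidepressants (25 h): "Hold 48–72 h before".
- Benzodiazepines (lorazepam 12–16 h, diazepam above 30 h): "Hold 24–72 h before".
- ACE inhibitors (11–24 h) and ARBs (up to 24 h): "Consider holding 24–48 h before".
- Beta-blockers (metoprolol 1–9 h, atenolol up to 24 h): "Reduce dose or hold 24 h prior".
- Antipsychotics (3–30 h, depending on the drug): "Review or suspend 48 h before".

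Nothing in the appendix says whether the sentence or the table prevails when they differ.

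**The concern.** A minimum in the text and shorter times in the table beneath it cannot both be the entry requirement. A centre working from the sentence and one working from the table would admit the same patient on different days, and the second could enrol someone who does not meet the stated minimum. The appendix gives safety during tilting as the reason for prohibiting these drugs, and orthostatic hypotension is one of the adverse events the trial records. At stake are consistent eligibility across the six centres and a modest safety margin at the first sessions.

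The action column raises a second difficulty. A lower dose, or a review, can leave the patient on a drug whose presence excludes them.

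**Working it through.** **Inputs.** The rule (four half-lives) comes from the Appendix B text. Half-lives and hold times come from Table A2. Where a hold is given as a range, the longest time is used, which favours the plan. For nitrates, stopping the day before is taken as 24 h (an assumption).

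**Formulas.** Required washout = 4 × half-life. Shortfall = required − longest hold. Longest half-life for which a hold meets the rule = hold / 4.

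**What the listed holds can cover.** 24 / 4 = 6 h; 48 / 4 = 12 h; 72 / 4 = 18 h. A drug with a longer half-life than this does not meet the rule at that hold.

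| Entry | Half-life (h) | 4 × half-life (h) | Longest hold (h) | Shortfall (h) |
|---|---|---|---|---|
| Alpha-blockers | about 22 | about 88 | 48 | about 40 |
| Tricyclics | 25 | 100 | 72 | 28 |
| Diazepam | >30 | >120 | 72 | >48 |
| Atenolol | up to 24 | up to 96 | 24 | up to 72 |
| Metoprolol | 1–9 | 4–36 | 24 | up to 12 |
| ACE inhibitors | 11–24 | 44–96 | 48 | up to 48 |
| ARBs | up to 24 | up to 96 | 48 | up to 48 |
| Antipsychotics | 3–30 | 12–120 | 48 | up to 72 |
| Furosemide, renal failure | up to 24 | up to 96 | 24 | up to 72 |
| Oxycodone | >12 | >48 | 48 | borderline |
| Lorazepam | 12–16 | 48–64 | 72 | none |
| Nitrates | 1–5 | 4–20 | 24 | none |
| Morphine | 2–4 | 8–16 | 48 | none |
| Furosemide, normal renal function | 1–1.5 | 4–6 | 24 | none |
| Dopaminergic agents | >6 | >24 | no time given | – |

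**Fails at the listed value (first three rows).** The longest holds are 48 / 22 = 2.2, 72 / 25 = 2.9 and less than 72 / 30 = 2.4 half-lives. If elimination is first-order (an assumption; the document does not state it), the fraction left is 2^(−hold / half-life): about 22%, 14% and more than 19%. Four half-lives leave 2^(−4) = 6.25%.

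**Fails only at the upper listed value (next six rows).** An ACE inhibitor at 11 h needs 44 h and complies with a 48 h hold. Metoprolol complies up to 6 h, and an antipsychotic up to 12 h.

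**Not failures at the longest hold.** Lorazepam needs 48–64 h, which lies inside its listed range of 24–72 h, so any hold of 64 h or more complies. Oxycodone at 48 h sits on the boundary and its shortfall cannot be quantified from an open-ended half-life.

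**The case against.** The best defence is that the rule can be identified. The sentence is worded as a minimum and is tied to an exclusion criterion, whereas the table column only recommends, often in tentative terms. Both can be met by taking the longer time. A class-level row also cannot give one correct time for half-lives of 3 to 30 h, so the per-drug sentence supplies the answer. This is largely right about which statement most naturally governs, but the appendix does not say so, and a recommended time below a stated minimum still conflicts with it.

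A second defence is that patients on these drugs at screening are ineligible, so the washout never matters. The same paragraph, however, provides for stopping before enrolment with a washout, and that washout decides when such a patient may enter.

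A third is that other safeguards limit exposure, and this stands. Inclusion requires at least four behavioural evaluations in one week. If the drug check comes first, some drug-free days would usually pass, although the order is not stated. T0 falls within a week of enrolment, tilting is gradual, and vital signs are monitored in each session.

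Three stronger readings might be inferred, and the documents do not support them:

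- **That Table A2 is a miscalculation.** The appendix never says its times were derived from four half-lives. It gives that basis only for the timings in Table A3, in softer wording. This is an inconsistency between text and table.
- **That most of the table fails.** Comparing the shortest hold in each range with the rule adds failures, but a range lets the clinician choose the longer time. Six of the nine entries with a shortfall also depend on the top of a range or an upper limit.
- **That the result is biased.** Any residual drug at enrolment precedes 1:1 randomisation stratified by centre.

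**Conclusion.** The inconsistency is real and minor. At the longest listed hold, three entries break the stated minimum at their listed half-life, by about 40 h (alpha-blockers), 28 h (tricyclics) and more than 48 h (diazepam). Six more break it only at the upper listed half-life, by up to 12 to 72 h. Separately, dose reduction (beta-blockers) and review (antipsychotics, dopaminergic agents) do not amount to a washout.

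The conclusion rests on the table's own half-lives, on reading the washout clause as a positive requirement counted from last dose to enrolment, and on taking the table's unspecified reference point as enrolment too. Holds repeated before each session cannot be meant, because these drugs may not be started or resumed between T0 and T2. If the table meant before the first session, the hold could begin after enrolment and the conflict would be larger.

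No endpoint, sample size, power or analysis depends on this point.

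**What to change.** State in the Appendix B text that the minimum of four half-lives, counted per drug from last dose to enrolment, prevails over Table A2. Then align the table:

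- about 88 h for alpha-blockers, 100 h for tricyclics and more than 120 h for diazepam;
- four times the individual drug's half-life for the other rows, including a time for dopaminergic agents (more than 24 h);
- a taper to stop, or discontinuation, in place of dose reduction and review, with the washout running from the last dose.

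If the shorter holds are clinically intended, withdraw the four-half-life minimum instead. That choice belongs to the sponsor's clinicians.

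The cost is appendix wording. Against the longest listed holds, entry is delayed by 12 to 72 h for the affected drugs at the half-lives shown, so about 3 days or less, and longer for diazepam if its half-life is well above 30 h. This is small against the entry window of 28 days to 6 months after injury.
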